# Study Schedule

Appendix A *Schedule of Procedures/Evaluations* contains the detailed schedule of observations and assessments to take place during the study.

## Screening

At the screening/baseline visit, the study will be fully explained to the subjects and written informed consent obtained from the subjects.

Subjects will be assessed as to whether they meet the inclusion/exclusion criteria. Patient who meet all criteria will be enrolled. Demographic details (age, sex, weight, height) and medical history and concomitant medication details will be recorded. Vital signs (pulse, blood pressure, respiratory rate, and temperature) will be taken. A physical exam will be performed and clinical signs and symptoms will be evaluated. Blood smears to confirm *P. falciparum* malaria will be performed. A blood sample will be taken for hematology, ALT and blood glucose analysis and a urine sample provided.

All female subjects between the age of 18 and 50 years will undergo a urine pregnancy test at baseline. They should either abstain from sexual relations or practice an acceptable method of contraception, such as an implant, injectable, or oral contraceptive(s). if possible with additional barrier contraception, intrauterine device, sexual abstinence, or vasectomized partner, throughout the study. Should pregnancy be suspected during the study the study subjects are advised to immediately notify the investigator. Pregnant women will not be eligible for entry into the study.

Blood samples will be drawn for parasite DNA molecular marker characterization and *in vitro* drug sensitivity analysis. Patient response to therapy will be monitored by assessing clinical parameters at baseline (Day 0) and daily at least until peripheral blood smears are negative for parasites. Plasma samples for determining drug levels will be collected from all patients at baseline and on Day 6*.*

## Follow-up and Final Visits

Patients will be admitted to the hospital (Tasanh Health Center) for the duration of study drug administration and followed closely with directly observed therapy and at least daily clinical assessment of their clinical condition and any potential emerging adverse events. They will remain in hospital for the full 7 days or until all signs and symptoms of malaria and/or any new gastrointestinal disturbances have disappeared, whichever is longer. Patients must regularly report for follow-up (at least on Days 14, 21, 28, 35, and 42) thereafter.

During hospitalization patients will have malaria smears performed up to four times a day until the smears are negative on 2 successive blood smears. Thereafter blood smears will be performed on Days 14, 21, 28, 35, and 42 or whenever signs and symptoms consistent with malaria reappear.

On Day 3, 6 and 14 hematology and ALT will be repeated (or whenever clinically warranted). Total RNA, *in vitro* and PCR samples will be collected in case of reemergence of parasitemia.

The time windows for the follow-up visits on Days 14, 21 and 35 are -2 to +6 days. Those on Days 28, and 42 are 0 to +6 days. Patients who do not attend the study site for follow-up will be contacted at their homes by study staff.

To maximize the scientific integrity of the study and patient safety, every effort will be made by study staff to contact patients missing follow up appointments. This may include telephone contact with subjects or visits to patient homes. Sample size calculations take into account a projected loss rate based on AFRIMS previous experience. Data and samples accrued from subjects subsequently lost to follow up will be stored and handled in the same fashion as the larger database including data from participants completing the study.

Patients who are found to have blood smears positive for *P. falciparum* malaria during follow-up who have received 6 or more artesunate doses will be treated with quinine/tetracycline according to national treatment guidelines for second-line treatment. These subjects will continue to be followed in the study until completion to ensure adequacy of treatment and completeness of their safety and tolerability follow-up.

## Compensation

During the first week patients will be provided with food, accommodation, and a daily compensation of 16,000 Riel (4000 Riel = 1 US Dollar). For the visits on Day 14, 21, 28, 35 and 42 patients will be provided 20,000 Riel for each visit and on Day 42 they will receive another 20,000 Riel for completing the entire study plus 4000 Riel for every day spent in the hospital. Patients will also be reimbursed for actual transportation costs for returning to the Health Center for follow-up patients. Patients completing the entire study and follow-up will receive a compensation of 260,000 Riel **(approximately $65)** plus reimbursement of actual transportation expenses. **This total reimbursement of about $5 per day is not felt to be high given that the subjects total time commitment to the study and follow-up leads to 13 days of lost work and compensation.**

## Criteria for Discontinuation or Withdrawal of a Subject

Any subject may be discontinued from the study at any time upon direction of the SMC, at the discretion of the investigator if he/she feels it is in the best interest of the subject (see Individual and Cohort Halting Rules, Sec 9.4.1-2) or if in the judgment of the investigator continuing in the study would be harmful and/or inappropriate for the subject (e.g. patients not tolerating the study drug, development of SAEs that require referral to another hospital) or if a patient cannot be followed thereby not permitting adequate safety assessment. Any patient who is terminated due to an SAE or unexpected AE will be reported to the medical monitor for review. Women who become pregnant during the trial will be taken off the study medicine and will be treated following the national treatment guidelines of Cambodia. If a woman becomes pregnant after the first 7 days she will be withdrawn form the study and will be followed for safety.

## Research-related Injuries

Medical care in case of research-related injury (including long-term medical care) will be provided free of charge according to local standard of care at the Tasanh Health Center. Subjects will only be treated for injuries that are directly caused by the research study. They will also be compensated for transportation to and from the hospital or clinic.

# Assessment of Outcome Measures

## Specification of the Appropriate Outcome Measures

Outcome measures for the clinical study is based on the criteria set forth by WHO in the “Assessment and Monitoring of Antimalarial Drug Efficacy for the Treatment of Uncomplicated Falciparum Malaria” for low to moderate transmission areas (WHO, 2003).

### Primary Outcome Measures (Clinical Outcomes)

PCR-corrected clinical outcome will be assessed for Day 28 and 42.

Classification of clinical outcomes:

- **Adequate Clinical and Parasitological Response (ACPR)**

• Absence of parasitemia on Day 28 and 42 irrespective of temperature without previously meeting any of the criteria of Early Treatment Failure or Late Clinical Failure or Late Parasitological Failure.

- **Early Treatment Failure (ETF)**

• Development of danger signs (e.g. impaired consciousness, convulsions, respiratory distress) or severe malaria on Day 1, Day 2 or Day 3, in the presence of parasitemia

• Parasitemia on Day 2 higher than Day 0 count irrespective of temperature

• Parasitemia on Day 3 with temperature ≥ 37.5 °C

• Parasitemia on Day 3 ≥ 25 % of count on Day 0.

- **Late Treatment Failure (LTF)**
  - Late Clinical Failure (LCF)

• Development of danger signs or severe malaria after Day 3 in the presence of parasitemia, without previously meeting any of the criteria of Early Treatment Failure

• Presence of parasitemia and temperature ≥ 37.5 °C (or history of fever) on any day from Day 4 to Day 28/42 without previously meeting any of the criteria of Early Treatment Failure

- - Late Parasitological Failure (LPF)

• Presence of parasitemia on any day from Day 7 to Day 42 and temperature < 37.5 °C, without previously meeting any of the criteria of Early Treatment Failure or Late Clinical Failure

### Primary Outcome Measures (Laboratory Outcomes)

Classification of laboratory outcomes.

- **Inhibitory Concentrations (ICs)**

• Inhibitory concentrations will be calculated by nonlinear regression analysis. The outcome is a continuous variable.

** Complete Blood Counts**

 Hemoglobin and white blood cell counts with differential to determine the absolute neutrophil count will be compared at designated time points between dosing arms.

### Primary Outcome Measures (Safety and Tolerability)

 Occurrence of treatment emergent adverse events both in total and in comparison of dosing arms will be determined.

### Secondary Outcome Measures

The secondary clinical endpoints are time until full clearance of parasites (parasite clearance time, PCT), gametocytes (gametocyte clearance time, GCT), and to disappearance of fever (fever clearance time, FCT: the time from start of treatment until the temperature drops to below 37.5 °C and remains below this temperature during the next 48 hours). The event time for clearance times is defined as the time until the first in a series of negative tests occurs. PCT, GCT, and FCT are continuous variables. The proportion of subjects still parasitemic on Day 3 (72 hours) will be calculated and compared with the other study sites.

# Safety assessment and reporting

An independent Safety Monitoring Committee (SMC) will be established. The prime responsibility of the SMC will be to assess and ensure the safety of patients in the high-dose cohort in comparison to the other two dosing arms,; its charter is given in Appendix C.

Adverse event assessment will be done throughout the study duration of 42 days. Treatment-emergent AEs for each patient will be documented daily on a standard form during the 7 days of in-patient artesunate treatment in addition to other routine AE assessments. These forms will be made available to the SMC for monitoring and review.

## Definition of Adverse Event (AE)

An AE is defined as any untoward medical occurrence in a subject undergoing a study related procedure and believed reasonably to be caused by that study related procedure.

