# Objectives

**3.1 PRIMARY OBJECTIVE:**

- The principal aim of this project is to determine the role of varying doses of artesunate for treatment outcome and whether higher doses of artesunate could overcome the problem of reduced artemisinin sensitivity in the region.
- To determine the safety and tolerability of this previously untested experimental high dose (6 mg/Kg/D X 7 day, total 42 mg/Kg) artesunate monotherapy regimen.

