## Definition of Serious Adverse Event (SAE)

An SAE is any untoward medical occurrence regardless of cause or relationship to study drug that:

- Results in death.
- Is life-threatening. Any adverse experience that places the subject, in the view of the investigator, at immediate risk of death from the reaction as it occurred (i.e., it does not include a reaction that, had it occurred in a more serious form, might have caused death).
- Requires in-patient hospitalization (excluding the hospitalization required by the study) or prolongation of existing hospitalization.
- Results in persistent or significant disability or incapacity.
- Is a congenital anomaly/birth defect.
- An event that required intervention to prevent permanent impairment or damage.
- Important medical events that do not result in death, are not life-threatening, or do not require hospitalization may be considered serious adverse events when, based upon appropriate medical judgment, they might jeopardize the subject and might require medical or surgical intervention to prevent one of the outcomes listed above.

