## Safety Reporting Procedures

All observed or volunteered adverse events regardless of treatment group or suspected causal relationship to study drug will be recorded on the adverse event pages of the case report form. Events involving adverse drug reactions, illnesses with onset during the study, or exacerbations of pre-existing illnesses other than malaria should be recorded. Exacerbation of pre-existing illness, including the disease under study, is defined as a manifestation (sign or symptom) of the illness that indicates a significant increase in the severity of the illness as compared to the severity noted at the start of the trial. It may include worsening or increase in severity of signs or symptoms of the illness, increase in frequency of signs and symptoms of an intermittent illness, or the appearance of a new manifestation/complication. Exacerbation of a pre-existing illness should be considered when a patient/subject requires new or additional concomitant drug or non-drug therapy for the treatment of that illness during the trial. Lack of or insufficient clinical response, benefit, efficacy, therapeutic effect, or pharmacologic action should not be recorded as an adverse event. The investigator must make the distinction between exacerbation of pre-existing illness and lack of therapeutic efficacy. In addition, clinically significant changes in physical examination findings and abnormal objective test findings (e.g., laboratory) should also be recorded as adverse events. The criteria for determining whether an abnormal objective test finding should be reported as an adverse event are as follows:

- test result is associated with accompanying symptoms, and/or
- test result requires additional diagnostic testing or medical/surgical intervention, and/or
- test result leads to a change in study dosing or discontinuation from the study, significant additional concomitant drug treatment or other therapy, and/or
- test result leads to any of the outcomes included in the definition of a serious adverse event, and/or
- test result is considered to be an adverse event by the investigator

Merely repeating an abnormal test, in the absence of any of the above conditions, does not meet conditions for reporting as an adverse event.

Any abnormal test result that is determined to be an error does not require reporting as an adverse event, even if it did meet one of the above conditions except for condition #4.

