# Appendix 1: Outline of contents for Safety Reports for the SMC ( to be prepared by the Principal Investigator and Medical Monitor)

The Safety report to be submitted to the SMC should contain the following information in a tabular format.

1. Summary of all Adverse Events

Template

| Adverse Event | Total | Grade | | | |
| --- | --- | --- | --- | --- | --- |
| 0 | 1 | 2 | 3 |
|  |  |  |  |  |  |

2. Summary of laboratory investigation

3. Grade 3 adverse events summary.

Template

| ID# | Gender | Date | Grade 3 AE | Start date | Resolution date | Causality | Action taken | Comments |
| --- | --- | --- | --- | --- | --- | --- | --- | --- |
|  |  |  |  |  |  |  |  |  |
|  |  |  |  |  |  |  |  |  |

4. Summary of SAEs

Template

| ID# | Gender | Date | SAE  (grade) | Start date | Resolution date | Causality | Action taken | Comments |
| --- | --- | --- | --- | --- | --- | --- | --- | --- |
|  |  |  |  |  |  |  |  |  |
|  |  |  |  |  |  |  |  |  |

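### Section 9.1 makes causation part of what an adverse event is, which contradicts the protocol's own recording rule and could let causality judgements filter a primary safety outcome

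*Protocol*

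**What the plan says.** Section 9.1 sets two conditions for an adverse event: the occurrence arises in a subject undergoing a study related procedure, and it is "believed reasonably to be caused by that study related procedure". It does not say who must hold that belief, or whether taking study drug is a procedure.

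Other parts of the protocol set no such condition:

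- Section 9.3: "All observed or volunteered adverse events regardless of treatment group or suspected causal relationship to study drug will be recorded". It also says that adverse drug reactions, "illnesses with onset during the study, or exacerbations of pre-existing illnesses other than malaria should be recorded".
- Section 9.2: "An SAE is any untoward medical occurrence regardless of cause or relationship to study drug that" meets one of the listed outcomes.
- SMC charter (Appendix C), section 1.2: the committee reviews all serious events and systemic grade 3 events, related or not. Under charter section 2.1 the investigator assesses causality for each adverse event, and may find none.

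Safety is a primary matter in this trial. One of the two aims in Section 3.1 is "To determine the safety and tolerability of this previously untested experimental high dose", the 6 mg/kg/day regimen. The safety and tolerability outcome in Section 8.1 reads: "Occurrence of treatment emergent adverse events both in total and in comparison of dosing arms will be determined". Section 9 says that the SMC's prime responsibility is the "safety of patients in the high-dose cohort in comparison to the other two dosing arms".

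**The concern.** A causality test inside the definition acts at the point of recording. An event that fails it may never reach the case report form, and an event not recorded cannot be recovered by any later analysis. A statistical analysis plan therefore cannot repair this.

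The trial is open label (Section 4), and the only blinded assessors the protocol names are the microscopists (Section 6.2.3). Anyone judging at the bedside whether an event was caused by the study would normally know the dose. The 6 mg/kg/day regimen is described as experimental and untested, so expectations about it could differ from those about the other two arms. If what counts as an event depends on such a judgement, the primary comparison between arms reflects the judgement as well as the events.

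**Working it through.** No figure in the protocol is at issue, so there is nothing to recalculate. The check is whether any reading of 9.1 agrees with the texts around it.

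**Reading A: procedure includes dosing.** An event judged unrelated to the drug and to every other procedure fails 9.1 and is not an adverse event. Section 9.3 says such events are to be recorded. Because 9.3 speaks of adverse events, a term that 9.1 has already restricted, its waiver of drug causality has almost nothing left to act on.

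**Reading B: procedure excludes dosing** (venipuncture, finger prick and the like). An event caused by the drug is then not caused by a procedure and fails 9.1. That removes adverse drug reactions, the first class of event that 9.3 lists and the class the primary safety outcome most needs.

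**Checks that apply on both readings.**

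| Text | What it requires | Compatible with 9.1? |
| --- | --- | --- |
| 9.3, illnesses with onset during the study | Recording, with no causality condition | No: an intercurrent illness judged unrelated fails 9.1 |
| 9.2, serious events | Any qualifying occurrence, whatever its cause | No: an event could be serious without being an adverse event |
| Charter 1.2, grade 3 events | Review whether related or not | No: an unrelated grade 3 adverse event could not exist |
| Charter 2.1, causality assessment | Made after the event is reported; may find no relation | No: under 9.1 belief in causation comes first |
| 8.1, treatment-emergent events | Selection by timing, compared by arm | Only if 9.1 has not already removed events |

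Section 9.3 also gives five criteria for treating an abnormal test result as an adverse event. None asks about cause. The fifth, however, defers to whether the investigator considers the result an adverse event, which leads back to the definition in 9.1.

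**From contradiction to consequence.** Two further steps are needed before the primary comparison is affected. First, staff must apply 9.1 over 9.3. Second, the share of events believed to be caused must differ by arm. If the share is the same in every arm, events are lost but no arm is favoured; if it differs, the recorded comparison is distorted. The protocol gives no attribution shares and no expected adverse event rates, so neither the size nor the direction can be calculated.

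**The case against.** The strongest reply is that 9.3, not 9.1, is the operative instruction. It tells staff to record regardless of suspected causality. Section 9 has treatment-emergent events documented daily for each patient on a standard form during the 7 days of treatment. The charter expects unrelated events to arrive, and the primary outcome is defined by timing. On this view a single sentence of definition would not override practice, and 9.1 does not even say whose belief counts. Much of this stands: filtering by unblinded staff is an inference from the open-label design, and it occurs only where 9.1 is followed literally. But the reply accepts that 9.1 is wrong as written, and nothing in the protocol says which section prevails.

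The effect on serious events is small. Sections 9.2 and 9.3.1 have them recorded and reported to the medical monitor whatever their relation to the drug.

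A reader might also infer that the SMC could not see an excess in the high-dose arm. The charter's Appendix 1 says "The Safety report to be submitted to the SMC should contain the following information in a tabular format", and its adverse event template has columns for total and grade but none for arm. The documents do not support that inference. The appendix is an outline of blank templates, and nothing says the summary must pool the arms. The SMC also has the daily patient forms (Section 9), a review specific to the high-dose cohort and the right to request more data (charter 4.3), and the cohort named in written event reports (charter 2.1). The cohort halting rules on individual halts and serious events work per arm (Section 9.4).

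**Conclusion.** The contradiction is established from the text alone and does not depend on how procedure is read. Section 9.1 cannot stand beside 9.2, 9.3 and the SMC charter. It should be corrected because it governs what is recorded for a primary safety outcome compared between arms without blinding.

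The consequence is conditional. It assumes that at least some staff apply 9.1 as written and that causality is judged by people who know the arm. A reader might infer that adverse event counts will be biased for or against the high dose; the documents show only that the wording permits this. They do not show that it would happen, how large it would be or which arm it would favour. Figures for lost power or false positives would rest wholly on assumed event rates and attribution shares, so none is given.

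The missing arm column in the SMC template is a weakness of the standing report. It is separate from the defect in 9.1 and minor.

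**What to change.** 1. Reword Section 9.1 along these lines: *any untoward medical occurrence from the first study procedure (Day 0) through Day 42, whether or not considered related to study drug or to a study procedure.* The period should start at the first procedure, not the first dose. Blood is drawn on admission before treatment (Section 4), bruising and infection at the puncture site are named risks (Potential Risks), and Appendix A schedules adverse event assessment from Day 0. The rule in 9.3 that lack of efficacy is not an adverse event can stay as it is.
2. Record relatedness as a separate field on the case report form, completed after the event has been entered.
3. State in Section 8.1 that the comparison between dosing arms uses all treatment-emergent adverse events, whatever their judged relatedness. The comparison itself is already planned.
4. As a minor, separate improvement, show the adverse event summary in the charter's Appendix 1 by arm with the number treated, and add an arm column to the grade 3 and serious event listings. Those two are line listings by subject, so they need no denominator.

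The cost is a sentence in each of 9.1 and 8.1, one case report form field, a few table columns and possibly slightly more event recording. Sample size and visit schedule are unaffected.
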